### Objectives {7}

In this RCT, we will assess the impact of the web-based serious game on iER skills in early adolescents. The primary objective of this study is to compare the improvement in pre- and post-intervention knowledge about iER strategies between a group that plays the intervention/serious game and a control group that plays a game without psychoeducational content. The secondary objectives are to examine sex differences in the use of specific strategies and to evaluate feasibility and acceptability of the intervention. We will examine the effects on outcomes of the following potential confounding variables: gender, prior gaming experience, language, and pER.

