## Intervention description {11a}

### Experimental intervention

An iER adventure game was/is currently being designed and developed using both scientific research and co-development workshops with children of the targeted age group to assure that the game has both learning and fun components. It is a single-player role-play/adventure game with 3 levels and a hub world (connecting the levels). It is played from a top-down perspective and created with the commercially available RPG Maker MV. The game is played on a phone or a browser. The game software will allow us to collect data on how the game was played, i.e. which options the participants chose and different time points (e.g. start time, end time). All conversations in the game will be presented in text through conversation windows. Total playtime depends on the player, as the explorative nature of the game allows more or less exploring, but to complete the game, approximately 3 h will be necessary. For the duration of the study, the game will be freely accessible (but will ask for a participant code to enter) via https://dot-game.picapipe.dev/.

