### Participant timeline {13}

This RCT adopts a pre-post-test strategy with the between-participant factor “group” and the within-participant factor “time”. Assessment will include pre-tests (questionnaires; day 1), intervention (playing the game; days 1–5), and post-tests (questionnaires and acceptability measures; days 5–10). After sending the consent forms, every participant will receive the link to the pre-test questionnaires via email. They take approximately  30 minutes to complete. At the end of these questionnaires, participants will be randomly assigned to either experimental or control group and receive the appropriate link for the corresponding game. Additionally, participants are asked to provide a unique identifying code consisting of the first letter of their own first name, the first letter of their mother’s first name, the first letter of their father’s first name, and the day of their birthday. They will use this code in the subsequent parts of the study to allow to link the parts anonymously. The link for the games can be opened as soon as they receive it and accessed with the unique identifying code that they used in the pre-test questionnaires already. Participants are asked to play the game for as long as they want but with the aim to finish it. After that, the participants have 5 days to play the game. They receive the link for post-test questionnaires 5 days after the first link was sent. The post-test questionnaires will take approximately 30 minutes to complete. After 2 days, a generalised reminder is sent to each participant via email to remind them to finish the study if they have not done so already.

The iER AG allows for great variability in playtime, but no matter how long each player takes to finish the game, everyone will have the same amount of iER interactions. As long as they play the game to the end, playtime has no influence on the psychoeducational component but only on the explorative “fun” part of the game. In general, we expect the average playtime to be approximately 3 h in total. The control group will get instructions to play the game as much as they want for the next days. They will receive the final questionnaires 5 days after they started the study. For an overview of the study design, see Fig. 1.

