## Assignment of interventions: allocation

### Sequence generation {16a}

After receiving the consent of a parent or legal guardian, the participant will receive a link to the pre-test questionnaires. At the end of the pre-test-questionnaires, participants will be randomised into either experimental or control group. We use SoSci Survey for administering the questionnaires via www.soscisurvey.de [38]. This software allows automated randomisation into different groups. We will use the option to “equally distribute” participants to avoid different group sizes. Depending on the group, participants will then receive the link to either intervention or control game directly in the questionnaire. Participants as well as researchers are blinded during the whole trial.

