*Gaming experience and preference*. Willingness to engage and hence outcomes might be influenced by gaming experience and gaming preference [47]. The style of the game in this study might remind some participants of games they already played as it is a common style in especially older AGs and some participants might have more experience. We will cover gaming experience with four questions specific to the current study: [1] Do you like videogames (answers are given on a 4-point scale: yes; rather yes, rather no, no)? [2] How much do you play per week (not at all (0 h); little (0–2 h); medium (3–5 h), a lot (more than 5 h))? [3] Have you ever played an adventure game (yes; no)? [4] If yes, what was the name (open question)?.

*Sociodemographic questions and questions to assess potential contamination*. Sex and age will be asked at the beginning of the questionnaires. After the intervention, participants will be shown a screenshot of the intervention game and asked if they have seen this game before. As we cannot gather data of the control game, we will additionally ask for how long the game was played approximately (0-30 min; 30 min–1 h; 1–2 h; more than 2 h). For an overview of the measures, see Table 4.

**Table 4 Tab4:** Measures used in the study

Measure	Assessment tool	Timepoint		
		Pre-test	In-game	Post-test
IER	Vignettes with hypothetical iER situations	x		x
ER	Emotion Regulation of Others and Self scale (EROS; 42)	x		x
Emotional competence	Emotional Skills and Competence Questionnaire (ESCQ; 44)	x		x
IER strategies	In-game option patterns		x	
Gaming experience	Self-developed questions	x		
Gender	Inventar zur Erfassung des Geschlechtsrollen-Selbstkonzepts im Jugendalter (GRI-JUG; 46)	x		
Acceptability	Game User Experience Satisfaction scale (GUESS-18; 45). In-game measures (drop-outs, time)		x	x

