#### Primary analysis—interpersonal emotion regulation skills

First, descriptive statistics will be generated for each observation time (pre- and post) and for each group: for continuous variables, mean and standard deviation (or median and interquartile range in case of a skewed distribution, respectively) and for categorical variables absolute and relative frequencies will be computed.

Answers of the vignette task will first be qualitatively assessed to exclude maladaptive as well as nonsensical strategies and merge answers that can be defined to be the same strategy. To analyse the main question, the change in the absolute number of positive strategies between pre- and post-test as well as the percentage of adolescents with a positive change in iER skills will be considered. A chi-square test (main analysis) will be calculated to compare the percentage between the two groups. Then, a logistic regression analysis will be performed for the dependent variable “positive change yes/no” to investigate the influence of the independent variables “time between last time of playtime and post-test”, “language”, “total playtime”, and “group”. To compare the change in absolute numbers, a non-parametric Wilcoxon rank-sum test will be performed (secondary analysis). The significance level will be set to 0.05.

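### The supporting logistic regression adjusts the group effect for two play variables that arise after randomisation, and one of them has no stated source in the control arm

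*Protocol article*

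**What the plan says.** The analysis of the primary outcome (Primary analysis, {20a}) has three steps.

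- The main one is an unadjusted comparison: "A chi-square test (main analysis) will be calculated to compare the percentage between the two groups".
- Next, "a logistic regression analysis will be performed for the dependent variable “positive change yes/no", to look at the influence of "time between last time of playtime and post-test”, “language”, “total playtime”, and “group".
- A Wilcoxon rank-sum test on the change in counts follows, labelled secondary.

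The other relevant statements are:

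- **Timing** (Sequence generation {16a}): "At the end of the pre-test-questionnaires, participants will be randomised into either experimental or control group". The game link is handed out only then.
- **Experimental-arm play data** (Experimental intervention): the software records "which options the participants chose and different time points (e.g. start time, end time". Completing the game is expected to take about 3 h.
- **Control-arm play data** (Secondary outcomes, sociodemographic and contamination questions): "As we cannot gather data of the control game, we will additionally ask for how long the game was played approximately". The answer is one of four bands, the highest being anything over 2 h. Neither this section nor Table 4 lists an item on when the control game was last played.
- **Missing data** ({20c}): no imputation.

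**The concern.** In a between-group model, a covariate measured after allocation can be part of the treatment's effect, or can share causes with the outcome. In either case the coefficient for group stops being the randomised comparison. Here two of the three covariates beside group are of that kind. They are also tied to allocation by design: one game has an ending about 3 h away, while the other can be played as much or as little as the participant likes.

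There is a more basic problem too. One of the two covariates appears to have no data at all in the control arm, which would leave the model without a group contrast.

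This is the only covariate-adjusted group comparison planned for the primary outcome, and it stands under the primary-analysis heading. Its group odds ratio is therefore likely to be read as the adjusted treatment effect. A null adjusted result beside a positive chi-square test, or the reverse, would confuse the trial's message.

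**Working it through.** **1. The plan's own figure.** Sample size {14} gives 62 per group for 30% against 10%, 80% power and level 0.05. Taking the test as two-sided with pooled variance and no continuity correction:

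n = [1.960·√(2·0.20·0.80) + 0.842·√(0.30·0.70 + 0.10·0.90)]² / 0.20² = [1.109 + 0.461]² / 0.04 = 61.6, so 62.

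For drop-out, 124 / 0.70 = 177.1, so 178, close to the stated 180. The figure reproduces. It rests on the unadjusted test, so nothing below changes it.

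**2. Can the group effect be estimated as written?** The model has five columns: intercept, interval, language, playtime and group. If the interval is missing for every control and is not imputed, a complete-case fit of 62 + 62 participants keeps 62 experimental and 0 control. Group then equals 1 for everyone left and duplicates the intercept. The design matrix has rank 4 for 5 columns, so the group coefficient is not estimable. This step needs no assumed effect or playtime, only that the interval is absent in the control arm.

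**3. What if the interval is dropped and playtime kept?** The documents give no expected control playtime, so the following are assumptions: mean playtime T of 2.5 h (experimental) and 1.0 h (control), SD 0.8 h in each arm, and a share s of the log-odds effect running through playtime. The planned rates fix the rest:

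- control log-odds: ln(0.10/0.90) = −2.197
- total effect: ln[(0.30/0.70) / (0.10/0.90)] = ln 3.86 = 1.350
- model: logit p = −2.197 + (1 − s)·1.350·group + s·(1.350/1.5)·(T − 1.0)

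Odds ratios come from a very large simulated sample, and power from 1,500 simulated trials with 62 per arm. Both fits include language.

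| Share s through playtime | Group OR without playtime | Group OR with playtime | Power without | Power with |
|---|---|---|---|---|
| 0% | 3.8 | 3.8 | 0.82 | 0.54 |
| 50% | 3.7 | 1.9 | 0.81 | 0.16 |
| 100% | 3.5 | 1.0 | 0.77 | 0.04 |

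Two hand checks agree:

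- At s = 50% the direct part is exp(0.5·1.350) = 1.96.
- At s = 0 the loss comes from collinearity alone. The variance of playtime between arms is 0.25·1.5² = 0.5625 and within arms 0.8² = 0.64, so the standard error for group grows by √(1.2025/0.64) = 1.37. A power of 0.82 corresponds to a z of 1.96 + 0.915 = 2.875. Then 2.875/1.37 = 2.10, which gives power of about 0.55.

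**4. Can playtime be made comparable between arms?** Control playtime is known only as a self-reported band with a top category starting at 2 h, below the roughly 3 h needed to finish the intervention game. Reducing both arms to these bands would put some non-finishers of the experimental game in the same category as finishers.

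**5. How many covariates can the model carry?** Expected improvers: 0.30·62 + 0.10·62 = 24.8, about 25 events. That supports only a short list.

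**The case against.** The strongest reply is that the trial's conclusion does not depend on this model. The abstract, the sample size and {20a} all make the unadjusted chi-square test the primary analysis. The design is called exploratory, and the regression is described as looking at influences rather than as the treatment-effect estimate. This stands, and it limits the severity.

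Several stronger readings are tempting, but the documents do not support them:

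- *That the primary comparison is compromised.* It is not. The chi-square test uses no play variable.
- *That no control participant will ever have a last-play time.* The article says control-game data cannot be gathered and names no substitute for this variable. A fuller questionnaire might contain one. What can be said is that no source is given.
- *That playtime is never a measure of exposure.* The statement "As long as they play the game to the end, playtime has no influence on the psychoeducational component" is conditional on finishing. Participants may stop when they like, and among non-finishers playtime can track exposure.
- *That the two arms necessarily measure playtime differently.* The duration item is not explicitly limited to controls. If it is asked of everyone, banded values would be comparable in form, but the limit of the top band remains.
- *That the objectives promise a different covariate set.* Objectives {7} says the effects of "potential confounding variables: gender, prior gaming experience, language, and pER" will be examined, but does not say in this model. Gender scores have their own regression in the secondary analyses.
- *That the bias has a known size.* It has not. If nothing runs through playtime and nothing else links it to the outcome, the odds ratio is about right and only power is lost.

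What remains is that the article itself fixes both the covariate list and the data sources, and the two do not fit together. That is not a detail left to a later analysis plan.

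**Conclusion.** The point holds for the supporting logistic regression only. As written, with no stated control-arm source for the last-play interval and no imputation, a complete-case fit cannot estimate the group effect. With the interval removed and playtime kept, the group coefficient does not estimate the effect of assignment.

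Under the assumed playtimes above, the consequence ranges from no bias with power reduced to 0.54, to complete loss of the effect (odds ratio 1.0, power 0.04). These sizes are illustrative. The non-estimability does not depend on them, but it does rest on the interval being uncollected in the control arm and on a complete-case fit. Severity: should be fixed.

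**What to change.** In {20a}, take total playtime and the interval from last play to post-test out of the between-group model. Fit group with language and the baseline number of adaptive strategies. Language is already on the plan's list, and the baseline count comes from the pre-test vignettes. With about 25 expected events, do not add more.

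Examine playtime and the last-play interval in a separate exploratory analysis within the experimental arm, where the game logs them, and label it as descriptive of play rather than of the treatment effect.

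The cost is one reworded passage in the analysis section, with no new data and no change in sample size. The loss is that the between-group model no longer describes the influence of the play variables across both arms. The article describes the trial as pre-recruitment, so the change can be made before any data exist.

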#### Secondary analyses

*Emotion regulation and emotional competence*. For the two questionnaires about emotion regulation and emotional competence, comparisons between groups will be performed for the pre-test and for the change between pre- and post-test (items change in the Likert scale is set to + 1 or − 1 if the Likert scale improves or worsens, by one point, respectively, and so forth). For both analyses, a Wilcoxon test will be performed.

*Sex differences within the experimental group*. Adaptive iER strategies will be dichotomised into positive engagement vs acceptance and for each participant the more frequent strategy will be determined. Our outcome variable is the proportion of which sex uses positive engagement (or acceptance). A chi-square test will be calculated to compare the percentage between the sexes. Second, a logistic regression analysis will be performed to evaluate if gender stereotype scores have an influence on the more frequent strategy positive engagement or acceptance. Note that for this analysis only adolescents from the experimental group will be considered.

*Feasibility*. Data from the feasibility questionnaire will be analysed using descriptive statistics. Open questions will be analysed qualitatively following thematic analysis [48].

For the secondary and exploratory analyses, the significance level for all tests is set to 0.05, *p*-values are interpreted in a descriptive manner. The statistical software programs R and SPSS will be used [49, 50].

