#### Sex differences in iER

Sex differences have been found in pER [6, 7], but data is lacking when it comes to iER specifically. In the general population, females seem to have better interpersonal skills than males, while males score higher on intrapersonal skills [8] and studies about related concepts such as emotional intelligence [9], emotional reliance [10], or coping [11] found sex differences.

To our knowledge, López-Pérez, Morillo [5] are the only ones who tested sex differences concerning specific iER strategies defined by classifications. They found that women tend to use positive engagement more often than men, which gives preliminary evidence that women engage in the social affective component of iER strategies more than men. In their study, age varied from 18 to 76, thus excluding the targeted group of our study. There might be stronger differences during adolescence when sexuality, and therefore also gender, starts to be an important topic [12].

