### Research questions

*Effectiveness*: How effective is playing the iER adventure game (AG) compared to a control group in terms of skills and knowledge regarding emotions and iER?*Sex differences*: Do boys and girls prefer different specific iER strategies according to Niven et al. (2009)’s classification?*Feasibility*: Is the iER AG feasible and acceptable in the targeted population?

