### Hypotheses

*Emotional skills*: Participants of the experimental group will be able to recall more adaptive iER strategies after playing the iER AG compared to the control group.*Emotional skills*: Participants of the experimental group will score higher on the Emotional Skills and Competence Questionnaire (ESCQ; Takšić et al., 2009) after the iER AG compared to baseline pre-test scores and compared to the control group.*Emotional skills*: Participants of the experimental group will score higher on the Emotion Regulation of Others and Self scale (EROS; Niven et al., 2011) after the iER AG compared to baseline pre-test scores and compared to the control group.*Sex differences*: In a computer animated game environment which requires players to use iER strategies in social interactions, male and female participants will prefer different iER strategies. Female participants are more likely to engage in positive engagement, whereas male participants are more likely to engage in acceptance.

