*Sex differences*. Sex differences will be examined in the experimental subgroup of our sample. During gameplay, the player undergoes 10 different scenarios, where they interact with NPCs by choosing one of up to four dialogue options. The four different strategies according to Niven, Totterdell [4] will be presented during these interactions. The dialogue options will consist of two adaptive and two maladaptive strategies (on average, with a range of 2–4 adaptive options, but always including both strategies of “positive engagement” and “acceptance”). Each picked option will be saved by the game, compiling an option pattern for each participant.

*Feasibility and acceptability*. For measuring feasibility, we will use the short version of the Game User Experience Satisfaction scale (GUESS-18 [45];). The scale has 18 items on a 7-point Likert scale (“strongly disagree” to “strongly agree”). It has 9 subscales (with two items each) covering aspects of gaming: usability/playability, narratives, play engrossment, enjoyment, creative freedom, audio aesthetics, personal gratification, social connectivity, and visual aesthetics. We will exclude the subscale “social connectivity” as the game is not a multiplayer game. Scores of different subscales can be added for an overall score. First validity measures show excellent convergent validity, with all subscales above 0.722. Reliability is *α* = .785 for the overall scale. In addition to the GUESS-18, we will analyse the time that was spent on the game and perform sensitivity analyses for drop-outs. The measure will be translated into German by the same procedure as described before.

*Gender*. Gender (in contrast to sex) will be assessed with the Inventar zur Erfassung des Geschlechtsrollen-Selbstkonzepts im Jugendalter (GRI-JUG [46];). This instrument assesses gender identity on four subscales: positive and negative feminine (communal; e.g. “emotional”, “vengeful”) and masculine (agentic; “companionable”, “lazy”) attributes. Each of the subscales consists of 5 items, yielding a total of 20 items. Subjects are asked to rate how much the attributes relate to themselves on a 5-point Likert scale (“does not apply at all” to “applies (nearly) always”). Internal consistencies of the scales are α = .81 (Mas+), *α* = .80 (Mas−), *α* = .88 (Fem+), and *α* = .74 (Fem−). Official English translation of the items exists.

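### The sex-difference analysis reduces four recorded strategies to one majority label per child over two clusters, so it cannot show differences within a cluster, loses information and ignores option supply

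*Protocol article*

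**What the plan says.** Four parts of the protocol article bear on this.

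- **Question.** Under Objectives {7}: "The secondary objectives are to examine sex differences in the use of specific strategies". Under Research questions: "Do boys and girls prefer different specific iER strategies", with reference to the classification in Table 1. That table has two clusters, each with two sub-clusters: affective and cognitive engagement under positive engagement, humour and attention under acceptance.
- **Hypothesis.** Under Hypotheses, the prediction is made for the two clusters: "Female participants are more likely to engage in positive engagement, whereas male participants are more likely to engage in acceptance".
- **Data.** Under Secondary outcomes (Sex differences): "During gameplay, the player undergoes 10 different scenarios". All four strategies appear in the course of play, and the software stores each option chosen. The mix of options is described as two adaptive and two maladaptive "on average, with a range of 2–4 adaptive options, but always including both strategies" (the two clusters).
- **Analysis.** Under Secondary analyses: "Adaptive iER strategies will be dichotomised into positive engagement vs acceptance". Each child is then labelled with the more frequent cluster, and the label is compared between the sexes by a chi-square test in the experimental arm. A logistic regression of the same label on gender-role scores follows. The significance level is 0.05 and p-values are read descriptively.

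**The concern.** The question is worded for specific strategies, and data at that level are saved, but the only planned sex comparison works on one binary label per child. Three things follow.

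1. A sex difference between two strategies of the same cluster leaves no trace in the label.
2. A child with six of ten picks in one cluster counts the same as a child with ten of ten. A child at five of ten has no majority at all.
3. The label takes no account of supply. A scenario with three adaptive options has to offer two from one cluster and one from the other, so a child choosing at random among them picks the larger cluster two times in three.

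At stake is how well a secondary objective is answered. A null result could be read as showing that boys and girls use the same strategies when only the cluster majority was compared. The percentage in each cluster could also be read as a preference when part of it may come from the script.

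**Working it through.** **The plan's own figure.** No sample size is given for the sex comparison, so the number of children has to come from the primary calculation (30% vs 10%, two-sided 0.05, 80% power):

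n = [1.96·√(2·0.20·0.80) + 0.8416·√(0.30·0.70 + 0.10·0.90)]² / 0.20² = 61.6, so 62 per group, as stated. That gives 62 completers in the experimental arm. I assume an equal split of 31 girls and 31 boys.

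**Further assumptions.** One adaptive pick in each of 10 scenarios, with picks independent. Where a scenario offers a positive-engagement and b acceptance options, P(positive engagement) = a·w/(a·w + b), where w is the per-option preference odds (w = 1 means no preference). Neither w nor the mix of a and b is in the document. Tied children are left out of the label test.

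**Ties.** With 1:1 options and w = 1, P(5–5) = 252/1024 = 24.6%. The other two classes have 37.7% each.

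**What the option description allows.** A mean of exactly two with a minimum of two forces two adaptive options in every scenario. Since both clusters are always present, every scenario is then 1:1 and supply has no effect. The upper end of the range fits only if the average is rounded. A mean below 2.5 means fewer than 25 adaptive options over 10 scenarios, so at most 4 beyond the minimum of 20.

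**Level under no preference (w = 1), extras all in positive engagement, share among non-tied children:**

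| Scenarios | Labelled positive engagement |
|---|---|
| ten 1:1 | 50% |
| nine 1:1, one 3:1 | 58% |
| eight 1:1, two 3:1 | 66% |
| seven 1:1, two 2:1, one 3:1 | 69% |
| six 1:1, four 2:1 | 71% |

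The last row is the maximum under the rounding bound. If the extras are all acceptance options, it mirrors to 29%.

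**Does supply create a false sex difference?** With w = 1 in both sexes, the label test rejected in 5.4% of 4,000 simulated trials with balanced options and in 5.3% with four 2:1 scenarios. It does not.

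**Power, girls w = 1.5, boys w = 1, 31 per sex:**

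| Options | Label, girls / boys (non-tied) | Non-tied n, girls / boys | Chi-square on label | Rank-sum on count (simulated) |
|---|---|---|---|---|
| ten 1:1 | 79% / 50% | 24.8 / 23.4 | 57% (simulated 58%) | 67% |
| six 1:1, four 2:1 | 91% / 71% | 26.5 / 23.9 | 43% (simulated 44%) | 64% |

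The non-tied n is 31·(1 − tie probability), for example 31·(1 − 0.201) = 24.8. The chi-square figures come from the two-proportion normal approximation with these n. The loss depends on direction: if the four extras are acceptance options, the labels are 60% and 29%, and the same formula gives about 59%.

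**Within-cluster differences.** Suppose girls' picks are 35% affective and 15% cognitive engagement, and boys' picks are the reverse. Positive engagement is 35% + 15% = 50% in both sexes. A 20-point difference on each of two strategies then gives no signal in the cluster endpoint.

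**The case against.** The strongest reply is that the analysis tests what was hypothesised. The prediction is stated for the two clusters, and the test compares those clusters. The background section also uses the phrase loosely: it describes earlier work as "the only ones who tested sex differences concerning specific iER strategies defined by classifications", and the result it then reports is for positive engagement, a cluster. **This stands.** The two-cluster contrast is legitimate. The gap is that the objective and research question are worded more broadly than the hypothesis and the analysis.

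Second, a reader might infer that option supply biases the sex comparison. The document does not support this. The participant timeline says that all players meet the same number of iER interactions, so supply is common to both sexes, and the null rejection rate stays near 5%. Larger shifts can be computed for 2:1 supply in five or all ten scenarios, but those need a mean of 2.5 or 3 adaptive options and do not fit the stated average of two.

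Third, the masking example is invented and extreme. If five scenarios offered affective and five cognitive engagement, 35% against 15% of all picks means 70% against 30% within each type, reversed between the sexes. Nothing in the document suggests such a pattern. **This also stands:** the example shows what the endpoint cannot see, not what is likely.

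Fourth, raw four-strategy shares would themselves depend on supply, because a scenario with two adaptive options can hold only one strategy per cluster. This is correct and shapes the fix.

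Finally, a four-strategy table and a rule for ties could sit in an analysis plan that is not shown. Their absence is therefore not the finding. The finding is that the article fixes a coarse endpoint for a question worded more finely.

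**Conclusion.** The point holds in a limited form. The planned label fits the cluster-level hypothesis but cannot answer a question about specific strategies, and it is a wasteful summary even of the cluster contrast. Under the assumptions above, it gives up about 10 points of power with balanced options (57% against 67%) and about 21 with four 2:1 scenarios (43% against 64%). A quarter of children without a preference fall on the tie when options are balanced.

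Supply can move the overall level by at most about 21 points, from 50% to 71% (or to 29%), and by nothing if every scenario has exactly two adaptive options. It does not produce a spurious sex difference, and it lowers power only when it pushes both sexes towards a ceiling or floor. The power figures rest on assumed preference odds, 31 children per sex and independent picks.

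The analysis is secondary, the trial is described as exploratory, and p-values are descriptive. Severity is low to moderate.

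**What to change.** In Statistical methods {20a}, sex differences within the experimental group:

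1. Keep the positive engagement versus acceptance contrast for the directional hypothesis, but compare the sexes on each child's share of positive-engagement picks minus the share expected from the options offered in the scenarios that the child answered, for example by a rank-sum test. For children who made adaptive picks in the same scenarios the adjustment is a constant and leaves the test unchanged. It matters where children answered different sets, and it makes the level interpretable.
2. Retain the chi-square test on the majority label as supportive.
3. Add a descriptive comparison of the four sub-cluster strategies by sex, each computed only over scenarios that offered that strategy.

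Under Secondary outcomes, reconcile the average of two adaptive options with the stated range, preferably by listing the number of options per cluster for each of the 10 scenarios.

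The cost is a few sentences and one table from choices that the game already saves. The downside is sparse cells for some of the four strategies, which is why that comparison should stay descriptive.
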